The evidence on the efficacy and effectiveness of suicide prevention strategies, such as Dialectical Behavioral Therapy (DBT), have been described (11–14). Indeed, DBT prioritizes suicidal behavior as the primary goal of treatment. In a meta-analysis of 18 RCTs, DeCou et al. demonstrated a significant pooled effect for DBT compared to control groups for self-directed violence (suicidal and NSSI behavior; *d* = −0.324, 95% CI = −0.471 to −0.176); however, there was no significant pooled effect of DBT for suicidal ideation (15). A more recent review, which evaluated the benefits and harms of psychological therapies for borderline personality disorder, identified DBT as having the largest number of primary trials, finding it to be the most effective psychotherapy at reducing self-harm (SMD-0.28, 95% CI-0.48 to-0.7; 7 trials, 376 participants) compared to TAU (16). Furthermore, in adolescents, 19 weeks of DBT was associated with a significantly lower frequency of self-harm episodes and suicidal ideation at post-treatment, 1 year, and 3 years follow-up (17, 18). In addition, some studies with similar results have added data regarding the feasibility of implementing DBT in adolescents, even at a community level, a necessary hallmark of the program (19, 20). Recently, a meta-analysis by Witt et al. concluded that there was a lower recurrence rate of self-harm (intentional self-harm) for adolescent DBT (30%) compared with treatment as usual, enhanced usual care, or alternative psychotherapy (43%) in repeated post-intervention self-harm in four trials (OR 0.46, 95% CI 0.26 to 0.82; *N* = 270; *k* = 4; high-certainty evidence) (21).

Despite this, and due to the short time to intervene in the suicidal process (22, 23), a crucial aspect of their effectiveness in daily practice is accessibility. This is why, beyond employing effective interventions to prevent suicide, they must be quickly available at the time of crisis.

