## Methods and analysis

### Trial design

This protocol describes the methodology of a parallel-group, two-arm randomized controlled trial, which will employ an intervention condition (CALMA app) and a control condition (Treatment as usual-TAU) with a 3-month follow-up for each participant. Participants will be assessed at four timepoints: day-0 (baseline), day-30, day-60, and day-90.

The intervention group will receive the CALMA app and continue with the usual treatment in a public hospital mental health service. The CALMA app will be downloaded with the assistance of a team member into the participant’s smartphone during the first interview. In each follow-up interview (30-days and 60-days), the use of the app will be reinforced. The control group (TAU) will not receive the app but will keep doing the usual treatment provided in public hospitals throughout the study. The usual treatment in public hospitals in Argentina consists of a weekly visit to a psychologist and a monthly visit to a psychiatrist (in case the patient receives any pharmacological treatment). In the public hospitals of Argentina, there are no DBT programs, and most of the interventions are psychoanalytic.

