### Intervention

#### Implementation of the intervention

CALMA is an app for smartphones that interacts with the user, providing evidence-based tools to prevent suicide; it is openly available and free to download on Apple or Google market place. It was developed, with contribution of mental health professionals, by our research group which are also mental health professionals. CALMA is based on the DBT program, which is one of the third-wave cognitive-behavioral therapies and seeks to train consultants with self-injurious behavior with and without suicidal intent in emotional regulation skills in order to manage their emotions more effectively (13, 55). CALMA integrates DBT strategies in two modalities: “Out of crisis” in which the user has some vulnerability reduction strategies to reduce the probability of crisis appearance, and the “I Need Help” modality (aimed at helping the user in crisis) constituted first with problem-solving strategies (DBT always gives the opportunity to solve the problem that triggered the crisis) and then, if the intensity of the crisis does not decrease, it implements distress tolerance or emotional regulation DBT skills dependent on the level of distress rated by the user (concept derived from the *breaking point* of DBT skills). A detailed description of the development of CALMA has been described elsewhere (51). All the features of CALMA app are based on face-to-face interventions that have shown efficacy in the reduction of self-injurious behavior and that are part of the central axis of the DBT program such as problem-solving (54), emotion regulation (13, 55, 56), distress tolerance (13, 55, 56) and also access to emergency contacts at the time of the crisis (31, 35). The app offers these interventions sequentially, and users can select which to employ. To guarantee the fidelity of the CALMA app to the model, DBT therapists have been included as stakeholders in the design of the intervention. Also, participants’ opinion was considered (52). In the management of an emotional crisis, the CALMA app follows the steps of crisis management and telephone coaching, initially going through the problem-solving strategy until reaching discomfort tolerance or emotional regulation skills as self-management strategies (11, 57, 58). The “Out of Crisis” modality consists of four functions that are identified in the initial screen of the app (Figure 1). The “Moments” function is based on the Inventory of Reasons to Live (59), considering that reasons for living reduce the risk of suicide (59, 60). In “Moments,” the user can add photos, videos, audios, songs, phrases, or anything that generates well-being and works as an anchor to life. The (b) “Agenda” function is based on evidence that positive events, such as pleasurable activities, serves as a protective factor for SI, thus reducing vulnerability to future suicidal crises (61). Moreover, engagement in positive events serves as a buffer between stressful adverse events and SI (62). The (c) “Profile” function provides the option for the user to add names and telephone numbers of people who can be contacted during a crisis if the crisis is not able to be resolved with the “Emergency Card” (see later). The (d) “Tips” function provides psychoeducational material related to suicidal crises and how to prevent unwanted behaviors during these crises. The user receives a weekly notification as a reminder of these sections. The “I need help” modality consists of interventions based on DBT skills. The skills were designed to be easily accessed during a crisis by the user activating the “I need help” button at the bottom of the home screen. All interventions are presented in a card format.

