### Participant timeline

Clinicians will be asked to draw up a list of patients who have presented self-injurious behavior in the last month. With this list, the patients will be identified on the days that they attend the control by their psychiatrist or psychologist of each Service. After the usual control of the patient, one of the members of the research group will explain the purpose of the study to the participant and legal guardian. Next, the researcher will give them a copy of the consent and/or assent to read carefully and invite them to participate in the study. After the invitation, those who agree to participate will be scheduled for a 30-min interview with one of the research group members.

The first interview will be face-to-face and it will determine if the participant meets the inclusion criteria and sign the informed consent. Then, a series of clinical and demographic data will be requested and the Spanish version of the Self-Injurious Thoughts and Behaviors Interview (SITBI) and the Difficulties in Emotion Regulation Scale (DERS) will be administered. At the end of the interview, the follow up interviews will be scheduled and those patients randomized to the intervention group will have the application downloaded to their cell phones. In addition, they will be given a brief 5 to 10-min tutorial on how the app works, they will be given written material on its functioning, and they will be directed to the website where there will be explanatory material.^1^

Follow-up interviews (day-30 and day-60): those will be conducted *via* video call according to the epidemiological context of the COVID-19 pandemic. During these calls, only the SITBI will be administered and participants will be asked if they have had any hospitalization due to suicidal behavior in that period, and if so, the date of admission. In the intervention group, to guarantee engagement with the CALMA app, the rater will explore whether or not the participant has used the application. In case of not using it, the obstacles and the alternatives to overcome them will be determined through a brief protocol (DBT missing links strategy) to reinforce the use of the application during the next evaluation period. At the same time, the technical team will work throughout the study to guarantee the proper functioning of the app.

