### Safety procedure

A strict suicide safety protocol will be followed given our participant eligibility criteria. Patient safety will be the highest priority in this study. Included in the CALMA app’s “Emergency Card” is a linked directory of major crisis helplines and a geolocation feature of emergency services near the user’s location, allowing participants to connect directly to these services.

A suicide safety assessment will be carried out in each interview, where the SITBI will be administered. Under the circumstance that the patient is at risk, the interviewer (a psychiatric member of the research group) will alert the parent and indicate that he/she accompany the participant to the Emergency Department of the center where the recruitment was carried out to be evaluated by a mental health professional. The interviewer also will alert the study coordinator ([name]) and will alert the research collaborator at each recruitment center. Each collaborator will immediately notify to the emergency room physician on call that day for an acute psychiatric assessment so that said clinician can contact the participant’s parent, guaranteeing the presence of the patient in the emergency department. In addition, each collaborator will notify the patient’s pediatric medical team of each hospital.

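### The suicide safety procedure lists the app's Emergency Card as a contact route for participants, but the expected 29 of 58 controls are not given the app; one contact sheet for both arms would close this modest gap

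*Protocol article*

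**What the plan says.** The Safety procedure section announces a strict suicide safety protocol. The first safeguard it describes is the app's Emergency Card, in which there "is a linked directory of major crisis helplines and a geolocation feature of emergency services near the user’s location, allowing participants to connect directly" to those services. The sentence sets no limit by arm. The section then says: "A suicide safety assessment will be carried out in each interview, where the SITBI will be administered". If that assessment shows risk, the interviewer alerts the parent and directs the family to the Emergency Department. The study coordinator, the site collaborator, the on-call physician and the pediatric team are then informed.

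Who holds the app is stated elsewhere. Trial design: "The control group (TAU) will not receive the app but will keep doing the usual treatment provided in public hospitals throughout the study". Participant timeline: "those patients randomized to the intervention group will have the application downloaded to their cell phones". Recruitment offers controls the app at the end of the study, and Patient and public involvement offers it after follow-up if results are positive. Under either statement they are not given it during the 90 days.

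Usual treatment in these hospitals "consists of a weekly visit to a psychologist and a monthly visit to a psychiatrist", the latter for patients on medication. Ethics and dissemination adds that all participants are treated by the Mental Health team during the study.

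**The concern.** A component of the experimental intervention sits inside the section meant to protect everyone in the trial. Read with Trial design and Participant timeline, that safeguard reaches one arm only. It is also the only route named in the section that a participant can start alone, between interviews.

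All participants are aged 10 to 19 and self-injured, made a suicidal gesture or attempted suicide in the month before entry. The protocol itself calls them high-risk. At stake is what control families have in hand if a crisis comes between appointments, and whether a reader of the safety section would think both arms are covered alike. The statistical comparison is not at stake.

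**Working it through.** This is mainly a comparison of sections, with a little arithmetic for size.

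**Planned numbers.** Sample size gives 25 per group before losses and 15% loss. 25 × 1.15 = 28.75, which rounds to the stated 29 per group. (Dividing instead, 25 / 0.85 = 29.4, gives 30; the difference does not matter here.) The total is 2 × 29 = 58.

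**Expected controls.** Randomization describes simple Bernoulli allocation with probability 0.5, so the number of controls is not fixed. The expectation is 58 × 0.5 = 29. The standard deviation is √(58 × 0.5 × 0.5) = 3.8, and the central 95% binomial range is 22 to 36.

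**Coverage of each stated safeguard during the 90 days.**

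| Safeguard | Intervention arm | Control arm | When it acts |
|---|---|---|---|
| Emergency Card (helplines, geolocation) | given | not given | any time, started by the user |
| Interview assessment and escalation | yes | yes | days 0, 30, 60 and 90 |
| Usual care, psychologist | yes | yes | about every 7 days |

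**Reading the table.** The last two rows are the same in both arms. Only the first differs, and it is the only one available on demand. Study interviews are 30 days apart (0, 30, 60, 90); psychologist visits are about 7 days apart. For a control outpatient, the usual gap between planned professional contacts is therefore about a week. Participants in hospital are already under hospital care, so the gap concerns outpatient time.

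**Effect of the remedy.** With one contact list for both arms, participants given a stated self-initiated contact route go from an expected 29 of 58 (50%) to 58 of 58 (100%). Sample size, alpha and power do not change.

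**What cannot be computed.** The document gives no basis for estimating how many crises would fall between contacts, so no number of events is claimed.

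**The case against.** The strongest reply is that the safety section says nothing false. The sentence is about a feature of the app and speaks of the user's location, so its participants can be read as those who have the app. Other sections are plain about who that is. The article also condenses a fuller protocol: ethics-approved consent forms exist and are not shown, and a helpline sheet may well be among them. This stands in part. It rules out saying that controls certainly receive no contacts, and it makes the remedy conditional. It does not remove the asymmetry that the text itself states, because the safety procedure uses an intervention-only feature as a safeguard and sets no limit by arm.

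A second reply is that controls stay in active treatment and that the app is public: "it is openly available and free to download on Apple or Google market place". The first half stands and keeps the weight modest. The second shows only that a control could find the app unprompted, which is not a trial safety provision.

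A third is that emergency-contact access is a declared part of the intervention, so a list for controls moves usual care slightly towards enhanced care. That is true, and it is the real cost of the remedy. Only the effect of contact numbers alone is lost; the DBT skills, the crisis-triggered card and geolocation stay in the contrast.

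Three stronger readings are tempting. A reader might infer that the protocol breaks its own standard, since the Introduction says that "beyond employing effective interventions to prevent suicide, they must be quickly available at the time of crisis". That sentence is the rationale for building an app and does not set a rule for monitoring trial participants. A reader might infer that loss to follow-up leaves controls worse placed, but interview-triggered steps stop for anyone lost, in either arm. A reader might also infer bias in the treatment comparison. The documents do not support that, because the Emergency Card is part of the package being tested against usual treatment.

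**Conclusion.** The point holds as a low-cost safety improvement of modest weight. As stated, the one self-initiated contact route in the safety procedure does not cover the controls, an expected 29 of 58 (plausible range 22 to 36). The remaining study steps cover both arms but begin only at interviews 30 days apart. Usual care at about weekly intervals fills much of that interval.

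This rests on two assumptions: that 58 participants are enrolled with allocation probability 0.5, and that no paper outside the article already gives both arms a contact list. If the second fails, what remains is a point of wording in the Safety procedure section.

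**What to change.** At the baseline interview, give every participant and guardian in both arms the same written list of helplines and local emergency services, with content set by the clinical team. In Safety procedure, state that the Emergency Card is a feature of the intervention arm, and that the written list and the interview-triggered escalation apply to both arms. Leave the objective, the comparator and the analysis as they are.

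The cost is one printed sheet and a short amendment. The baseline visit already includes handing out paper about the app to the intervention arm: "they will be given written material on its functioning". The sheet would also serve intervention participants who do not open the app, or whose crisis does not reach the card, which appears only if distress worsens or has not eased after three attempts. If the consent or baseline papers already supply such a list to both arms, make only the change in wording.

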### Patient and public involvement

In the previous CALMA pilot study carried out by this research group, feedback was collected with the experiences and preferences of the participants in the intervention group, which have been taken into account for the current version of the app. Patients were not involved in other aspects of the design, or conduct, or reporting, or dissemination plans of our research. In case the current study shows positive results, the app will be downloaded to the smartphones of the control group participants for use after follow-up.

## Discussion

Smartphones provide promising opportunities for wider dissemination of and access to suicide prevention interventions by improving help-seeking behavior and providing low-cost real-time help (48). There are backgrounds of interactive apps with DBT tools, such as DBT Coach, but designed specifically to augment skills generalization through interactive coaching in DBT skills as an adjunct to standard DBT. Particularly, use of the DBT Coach was not related to any treatment outcomes, except for reductions in NSSI (76). Others apps have incorporated behavioral interventions such as a diary as an adjunct to DBT treatment (77). In the same line, Schiffler et al. have shown the implementation of a Mobile DBT App for young adults (aged 18 to 23 years) with a focus on suicidality and NSSI, in a natural setting, without showing effectiveness results (78).

A recent systematic review measured the effectiveness of mobile apps for Monitoring and Management of Suicide Crisis (79). Of the 32 included studies, 16 evaluated feasibility and acceptability of those mobile apps, 10 studies assessed the effectiveness of mobile app in preventing suicide and six studies described randomized control trial protocols not yet implemented. Most of the studies took place in Europe (*n* = 13) and the United States (*n* = 9); only two of them were about apps in Spanish. First, MEmind, a tracking non-intervention mobile app with EMA (Ecological Momentary Assessment), and CALMA. Of the 16 studies that evaluated feasibility and acceptability, four included adolescents with suicidal ideation or behaviors, some of which included DBT skills within their features or personal problem-solving strategies. Two of them also included adults, and only the other two focused specifically on adolescents. Of the 10 efficacy studies, two included adolescents who attempted suicide. The first was a one group pre–post test pilot study with only 3 participants. The second one, an RCT of 66 hospitalized suicidal adolescents that reported no significant differences in suicidal outcomes. It is worth clarifying that the intervention was a face-to-face plus a mobile app after discharge intervention.

In a prior pilot study, the CALMA app has shown initial evidence of safety and acceptability of the app for reducing self-injurious thoughts and behaviors when used as an adjunct to conventional DBT therapy within 4 weeks of follow-up (52). This study has shown good acceptability of CALMA as an adjunct to therapy targeting suicidal and non-suicidal self-injured behaviors. Furthermore, a high probability of decreased in SI, suicidal plan, suicidal gesture, thoughts about Non-Suicidal Self-Injury (NSSI) and NSSI pre-and post-intervention was observed in the group that received CALMA and a high probability of a greater decrease in SI and suicidal gesture before and after the intervention for the group that received CALMA compared to the comparison group.

This protocol describes a parallel-arm randomized controlled trial, which aims to test the efficacy, safety and acceptability of the CALMA application as an adjunct to therapy to reduce suicidal and non-suicidal self-injurious behaviors in adolescents.

This research will fill important gaps about the engagement and effectiveness of a DBT skills-based application in adolescents. Firstly, there are few studies of apps that focus on adolescents with suicidal behaviors, a population at higher risk of suicide and with distinctive characteristics (80); only some have the characteristic of being interactive with the user. Second, of the few studies that did measure effectiveness in this population, the results were negative. Third, this study is particularly relevant to young people given their widespread use of mobile technology, while there are currently no available mobile applications in Spanish at all that attempt to reduce suicidal behavior in this population (35, 81). Fourth, having a tool that can help reduce the probability of hospitalization for suicidal behavior that is economical, universal, and that is at the service of the crisis, such as an application, would undoubtedly democratize access to specific and effective intervention. Fifth, if the exploratory objective of this study demonstrates that the reduction of self-injurious behaviors is mediated by the improvement of emotional regulation, an app such as CALMA can be an invaluable tool to increase the capacity (skills) to manage intense and painful emotions.

The potential benefits for patients who have the app are that they will have a helpful tool to resolve self-injurious crises. In addition, if the study demonstrates the app’s effectiveness, the results may have potential benefits from a social point of view, since the app will be free to use.

In addition, this evidence will be important to add an innovative and alternative tool to the treatment of suicidal behavior in this population in the public health sector, especially from low and middle-income countries in Latin America, since no study at all was carried out in this region of the world.

Smartphone app-based self-guided psychological strategies for suicidal thoughts and behaviors have the potential to increase access to treatment and reduce barriers to help-seeking by providing accessible, anonymous and timely support, which could then reduce suicide risk, especially in scenarios like the COVID-19 pandemic (47, 82, 83).

